### Baseline assessment

The baseline assessment (day 1) will be scheduled immediately after screening. At baseline, the following tasks will be performed:Review and record all prior workup or test results.Record detailed history of prior medication use in the subject.The query for signs and symptoms and updated medications used since the screening visit. Any signs or symptoms reported after study drug administration should be recorded as adverse events. Any signs or symptoms reported before the study should be recorded as a pre-existing condition but should be collected and recorded in detail.Perform a complete physical examination.Obtain vital signs (HR, BP, RR, Oxygen saturation, capillary refill), Oxygen saturation (SpO2) with pulse oximetry.Obtain body height, weight, and waist circumference.Obtain the dietary history of the patients.Collect urine for urinalysis, with the microscopic exam and for a pregnancy test (in women).Collect blood for CBC and for serum chemistries including creatinine, total bilirubin, albumin, ALT, AST, total protein, CK, Creatinine Clearance (CrCl), and Ab assays, fasting blood sugar, lipid profiles (TC, LDL, HDL and triglycerides), plasm 25-hydroxy vitamin D concentration, laboratory test for D-dimers, platelet count, PT PPT, INR, and serum ferritin.Collect serum (recommend 5 mL serum storage at the investigational site as a back-up specimen).

### Follow-up visits

Data collection at follow-up at 2 weeks, 3 months, 6 months, 9 months and 12 months was the same as at baseline and used to ascertain primary and secondary outcomes. The following tasks will be performed at these visits:Perform symptom-Directed physical exam,Obtain body weight and vital signs including pulse, respiratory rate and blood pleasure, oxygen saturation,Perform pulmonary function test (PFT),Record any symptoms,Spirometry to determine pulmonary function tests such as forced expiratory volume in the first second (FEV1), forced vital capacity (FVC) and FEV1/FVC ratio,Collect blood for serum chemistries including creatinine, electrolytes, total bilirubin, albumin, ALT, AST, total protein, CK, calculate CrCl, Ab tests,Collect mouth/nasal swabs for PCR tests,Collect urine for analysis, including pregnancy test (in women),Collect serum on-site as the back-up storage (3 mL serum) andCollect dietary history.

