### Sample size and sampling procedures

The estimated sample size for this study is 6,390, based on the assumptions of a 28 percent death rate from a retrospective study, a design effect of 2.5, and a 20 percent loss to follow-up. A baseline evaluation or assessment will be performed immediately after screening. After baseline assessment, all patients will be followed-up daily until discharge according to WHO and National discharging guideline and followed as per schedule after discharged. Study subjects enrolled will be followed up for 12 months after enrollment for the specific objective related to virology and immunology, clinical course of the disease, response to treatment, effect of COVID-19 in pregnant mothers and birth-related effects of COVID-19. Enrolled cases will be followed up at 2 weeks, 3 months, 6 months, 9 months, and 12 months post-discharge. A visit window of ± 7 days may be applied to these visits. Patients discharged after recovery will be followed up according to the follow-up schedule.

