### Primary outcome and secondary outcomes

The primary outcome variables are treatment outcome (active cases, recovered, death or transferred for further treatment), recovery time, and duration of viral shedding (the time from the first positive RT-PCR results to the occurrence of the last positive RT-PCR results or negative RT-PCR results). The secondary outcomes include clinical symptoms and signs (major); co-morbidities; status at last follow-up (survival, severity, virus detection); laboratory biomarkers; duration of symptomatic phase, inpatient stay, ICU stay; viral loads; anti-SARS-CoV-2 antibody titer; imaging with results; therapeutic measures; plasma 25-hydroxyvitamin D concentrations; dietary history; micronutrient status (zinc and vitamin A); fasting blood sugar; weight, height, BMI; total cholesterol (TC), triglycerides (TG), HDL-C, LDL-C and body composition(waist circumference); genetic frequency shifts (genotypic variations); obstetric and gynecologic history; pregnancy status/test; clinical status; supplemental oxygen; non-invasive ventilation or oxygen delivery devices/ respiratory support. We will also collect confounding variables include socio-demographic variables (age, sex, education status); status cases at the time of enrollment; and months after the first positive test.

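### The follow-up section says visits repeat baseline, then lists different tasks without medication history; vaccination is named nowhere, so 12-month antibody and treatment-response results could be confounded

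*Protocol article*

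**What the plan says.** The Follow-up visits section of the protocol article states that collection at 2 weeks and at 3, 6, 9 and 12 months "was the same as at baseline and used to ascertain primary and secondary outcomes". The next sentence starts a specific list, "The following tasks will be performed at these visits:Perform symptom-Directed physical exam", which ends with "Collect serum on-site as the back-up storage (3 mL serum) andCollect dietary history". Antibody testing is in that list ("total protein, CK, calculate CrCl, Ab tests"). No medication item is.

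The Baseline assessment section has two medication items: "Record detailed history of prior medication use in the subject" and "The query for signs and symptoms and updated medications used since the screening visit". The screening paragraph under Data collection also takes concomitant medication histories.

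Under Primary outcome and secondary outcomes, the secondary outcomes include "anti-SARS-CoV-2 antibody titer" and therapeutic measures. The confounders named there are socio-demographic variables, status at enrolment and months since the first positive test. Sample size and sampling procedures says that participants are "followed up for 12 months after enrollment for the specific objective related to virology and immunology", and names response to treatment among the other 12-month objectives. No section mentions vaccination.

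**The concern.** Both statements in the follow-up section cannot be followed. A site that relies on the opening sentence repeats the medication questions at every visit. A site that works from the list never asks them after discharge. With many treatment centers, different readings could also make the data differ by center.

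Antibody titre can change for reasons other than the natural course of infection, and vaccination is the obvious one. If vaccination and its date are unknown, a titre that rises or fails to fall could be a vaccine response, lasting natural immunity or reinfection. Any comparison of traditional and modern treatment that extends past discharge likewise needs to know what was taken after discharge. The named confounders cover neither exposure. The check for omitted-variable bias promised under Data processing and statistical analysis cannot adjust for a variable that was not collected.

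**Working it through.** **Step 1: the sections side by side.**

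| Item | Screening or baseline | Follow-up list |
|---|---|---|
| Medication history | Yes, at both | Not listed |
| Physical examination | Complete | Symptom-directed |
| CBC, fasting glucose, lipids, vitamin D, D-dimer and coagulation, ferritin, waist circumference | Yes, at baseline | Not listed |
| Lung function, electrolytes, PCR swabs | Not in baseline list | Listed |
| Antibody tests | Yes | Yes |
| Dietary history | Yes | Yes |
| Supplements | Not named | Not named |
| COVID-19 vaccination | Not named | Not named |

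Three things follow.

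- The follow-up list is a separate schedule. It drops some items, changes others and adds new ones, down to the stored serum volume (3 mL, against 5 mL at baseline). It cannot be read as shorthand for repeating baseline.
- Medication is a true contradiction, because baseline has it and the list does not.
- Vaccination is an omission. It is absent from baseline too, so reading follow-up as a repeat of baseline would restore medication but would not add vaccination.

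**Step 2: how large could the effect on titre be?** The plan has no figure to reproduce here, and its sample size does not bear on the point. Every input below is an assumption from outside the documents:

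- natural titre half-life T = 120 days;
- vaccination multiplies titre by B = 10;
- a fraction p of 5%, 20% or 30% is vaccinated between months 6 and 12 (183 days).

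True ratio of the month-12 to the month-6 titre: 2^(−183/120) = 0.347, a fall of 0.459 on the log10 scale.

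Inflation of the month-12 geometric mean: B^p = 10^p, since a fraction p of the log titres each rise by log10(10) = 1.

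Observed ratio: 0.347 × 10^p. Share of the log decline hidden: p × log10(B) / 0.459 = p / 0.459.

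| p | Inflation | Observed ratio (true 0.347) | Log decline hidden |
|---|---|---|---|
| 5% | 1.12 | 0.39 | 11% |
| 20% | 1.58 | 0.55 | 44% |
| 30% | 2.00 | 0.69 | 65% |

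The hidden share is proportional to uptake, to the log of the boost and to the half-life. Halving either of the last two halves it: at 20% uptake, 44% becomes 22%. The table shows sensitivity and is not a forecast.

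No comparable calculation is possible for medication, because the documents give nothing on use after discharge or its effect.

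**The case against.** The strongest reply is that the text is ambiguous and does not show a gap. If the opening sentence governs, medication is asked at every visit. Follow-up is also said to ascertain the secondary outcomes, and therapeutic measures is one of them. Study design and period promises extensive routine collection of clinical management data. Data collection refers to a questionnaire and case report form, which are not shown, and a condensed article may leave such items to them. This stands to the extent that nobody can say from the article that later treatment goes unrecorded. It does not remove the contradiction, which is in the text shown.

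Second, the contradiction concerns medication, while the illustrative figures concern vaccination. That is correct, and the two parts should be kept apart. Supplements are weaker still, since the dietary history taken at follow-up may capture them.

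Third, a reader might infer that missing vaccine dates could never be recovered. The documents do not support that. Back-up serum is stored at follow-up visits and could permit later assays, and contact details are held, so dates could be sought retrospectively with some recall error. Recovery would be partial but is possible.

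Fourth, a reader might infer that the treatment effects are shown to be misclassified. They are not. The treatment aim concerns admitted patients, who are followed daily until discharge, and much of the treatment outcome and recovery time arises in or near the admission. Only the part of treatment response measured after discharge is at risk.

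**Conclusion.** The point holds as a contradiction to be reconciled and a conditional risk of bias. The follow-up section is inconsistent on whether visits repeat baseline, with medication among the items lost, and the article nowhere provides for recording vaccination.

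Confounding of the 12-month antibody and treatment-response results requires both that the exposures are in fact not recorded with dates and that participants are treated or vaccinated after discharge. The documents settle neither. It would therefore be too strong to say that these results do mix disease with later treatment. Under the stated assumptions the inflation of the 12-month geometric mean runs from 1.12 to 2.00 times, but uptake, boost and half-life are all assumed, so the range should not be quoted as a property of this study. The point is worth acting on because the correction is cheap and dates are best recorded at the visits themselves.

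**What to change.** 1. Reconcile Follow-up visits with Baseline assessment. State which list governs, and have each follow-up visit record medicines and traditional remedies taken since the last visit, with start and stop dates. Settle the other dropped items in the same edit.
2. Add COVID-19 vaccination (date, product, dose number) at baseline and at each follow-up visit, or confirm that the case report form already holds it.
3. In the natural-course antibody analysis, censor titres at the first vaccine dose after infection, or model vaccination as a time-varying covariate. If the unseen analysis plan already has such a rule, a cross-reference is enough.

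The cost is a few form fields at visits already scheduled and one analysis rule. The downside of censoring is fewer late titres in the natural-course curve. These changes concern data collection and analysis only and leave patient management as it is.

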### Data processing and statistical analysis

Data collection will be done electronically using the ODK software package and then exported to STATA/SPSS for data cleaning, management, and statistical analysis. The data will be cleaned and checked for outliers, all assumptions, and analyzed using appropriate statistical software (STATA, Python, and/or R statistic software).The analysis will be performed by trained personnel (epidemiologists, statisticians, health economists) using the appropriate statistical methods. Statistical analyses strategy will be based on specific study objectives and the nature of the outcome variables, the various assumptions to be assessed and associated scenarios to be considered, and the criteria to be used for decision-making at each stage including management of incomplete data, model building procedures, and evaluating the validity of models and the robustness of results. Data will be assessed for consistency, missing values, presence of outliers and implausible values, and different statistical assumptions including univariate and multivariate normality of distributions, the linearity of hypothesized relationships, the proportionality of hazard, and the presence of rare events among others.

A descriptive summary of the continuous variables will be reported as mean (± SD) and median (IQR), and categorical variables will be summarized as counts and percentages. A correlation or chi-square test will be performed for appropriate variables.

Predictors that have been identified as risk factors in the bivariate analysis will be entered into multivariable analysis to isolate independent determinants of the outcome. Multiple linear and generalized linear regression models will be fitted depending on the type of outcome variable. Cox-proportional hazard ratio (HR) will be used for time-to-event variables including the time to recovery, and other time to event variables. Time to event analysis, semi and parametric survival analysis will be conducted as appropriate.

To take into account the multi-center cohort design, i.e., clustering of data by treatment centers and repeated measurements per subject over time, a multilevel modeling approach will be employed using mixed-effects modeling or generalized estimating equation. Incomplete data (missing values and lost-to-follow-up cases) will be handled using model-based approaches, such as full information maximum likelihood estimation and multiple imputation modeling after the missing data mechanisms and assumptions are evaluated. Regression models will be evaluated for potential problems including collinearity among predictors, omitted variables bias, and model over-adjustment (endogeneity). The final fitted models will be assessed for validity and robustness of results on a subsample of data not used in the model-building procedure. For this purpose, a random subsample from the original data will be kept before starting the analysis. Statistical significance will be considered at α < 0.05. However, to control for the inflated probability of Type-I error due to multiple hypotheses testing, P-values will be adjusted for false discovery rate using the Benjamini–Hochberg method. The results will be described as percentages, tables, figures, and association significance.

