## Methods/design

### Aim and study setting

In this multi-site cohort study, we aimed to determine the natural history of the disease; clinical features and management, epidemiological characteristics, immunological, virological courses and treatment response of the disease, effects of diets on the nutritional status on the disease progression, effect of the disease on pregnancy and birth outcomes, and the effect of traditional/modern treatment on COVID-19 outcomes among patients admitted to treatment centers in Ethiopia. Therefore, the study findings will generate scientific data for a systematic understanding of natural history, epidemiological characteristics, clinical features, and management of COVID-19 which will, in turn, enable the country’s health sector to develop strategies to prevent and control the pandemic before it poses further health and socioeconomic crises. The research question of this study is “Do different individual host factors and environmental situations influence clinical, epidemiological, and viral outcomes of COVID-19 infection?”.

The study will be conducted in all Federal treatment centers, including Ekakotebe, Yekatit-12, St. Peter Specialized hospitals, SPHMMC, Millennium hall center in Addis Ababa, and Regional Hospitals including Mekelle, Semera, Bahir Dar, Adama/Mojo, Hawassa, Jijiga, Harar, DireDawa, Metekel or Benishangul Gumuz, and Gambela dedicated to COVID 19 treatment.

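### GEE is allowed without condition for clustering by about 15 listed centres; with the usual uncorrected sandwich errors, type I error would be about 8-12% (patient-level) or 8-20% (centre-level) rather than 5%

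*Protocol article*

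**What the plan says.** The protocol article, under Data processing and statistical analysis, names two sources of dependence, "clustering of data by treatment centers and repeated measurements per subject over time", and answers both with one clause: "a multilevel modeling approach will be employed using mixed-effects modeling or generalized estimating equation". It gives no working correlation, variance estimator, cluster unit for GEE or small-sample correction. The same paragraph sets the threshold, "Statistical significance will be considered at α < 0.05", and then applies a Benjamini-Hochberg adjustment for multiple testing.

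Aim and study setting lists the sites. The federal ones are given as "including Ekakotebe, Yekatit-12, St. Peter Specialized hospitals, SPHMMC, Millennium hall center in Addis Ababa", which is five. The regional ones are "Mekelle, Semera, Bahir Dar, Adama/Mojo, Hawassa, Jijiga, Harar, DireDawa, Metekel or Benishangul Gumuz, and Gambela", which is ten entries. Both lists are introduced as inclusive, so a few more sites are possible.

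Sample size and sampling procedures states: "The estimated sample size for this study is 6,390, based on the assumptions of a 28 percent death rate from a retrospective study", with "a design effect of 2.5, and a 20 percent loss to follow-up".

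**The concern.** The ordinary GEE sandwich variance is a large-sample estimator in the number of clusters, not the number of patients. With 6,390 patients in about 15 centres, GEE clustered on centre has about 15 independent units. Used with normal critical values, the uncorrected sandwich is then biased low and too variable, so intervals are too narrow and p-values too small. At this number of clusters GEE and a random-intercept model are not like-for-like substitutes, yet the text joins them with a plain alternative.

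The study tests many predictors across many outcomes. Benjamini-Hochberg controls the false discovery rate only if each null p-value falls below a given threshold no more often than it should. If 8-12% of null p-values fall below 0.05, that premise fails before the adjustment starts. The planned check on a held-out random subsample does not help either: it draws on the same centres, so a chance association between centres would tend to reappear in it.

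**Working it through.** **Inputs from the article.** Centres: 5 + 10 = 15 (16 if Adama/Mojo counts as two). N = 6,390, death rate 0.28, design effect 2.5, loss 20%, alpha 0.05 (two-sided assumed).

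**The plan's own figure.** The article states no type I error for GEE. The related figure is N. For a single proportion, n = z² p(1-p)/d², times 2.5, then inflated for loss. Precision d and confidence level are not given. At 95% and d = 2%: 3.8416 × 0.2016/0.0004 = 1,936; × 2.5 = 4,840; then 6,051 (÷ 0.8) or 5,808 (× 1.2). Back-solving with z = 2.57, d = 2.5% and × 1.2 gives 6,391, against 6,390. Nothing below depends on which was used.

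**Implied intracentre correlation.** Design effect = 1 + (m - 1) × ICC, with equal centres.
- All enrolled: m = 6,390/15 = 426; ICC = 1.5/425 = 0.0035.
- After loss: 6,390 × 0.8 = 5,112; m = 5,112/15 = 340.8; ICC = 1.5/339.8 = 0.0044.

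**Analytic reference.** If the statistic behaves like t with 14 degrees of freedom, P(|t| > 1.96) = 7.0%. Allowing also for a sandwich bias factor of 14/15 in the variance, P(|t| > 1.96 × √(14/15)) = 7.9%. The ICC does not enter: the number of clusters drives the inflation.

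**Simulation.** Logistic GEE clustered on 15 centres, 5,112 patients, death rate 0.28, no true effect, uncorrected sandwich, critical value 1.96. Assumed: ICC 0.0044, 0.02 and 0.05; coefficient of variation (CV) of centre size 0, 0.6 and 1.0; independence and exchangeable working correlation; 2,000 runs per setting. The GEE code agreed with a standard package on a test data set.

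| Predictor | Equal sizes | Unequal sizes |
|---|---|---|
| Patient-level | 7.4-10.5% (mostly 7.5-8.5%) | 8-12.5% at CV 0.6; 9.4-16% at CV 1.0 |
| Centre-level, 7/8 split | 9-10% | up to 17% at CV 1.0 |
| Centre-level, 5/10 split | 11-12% | 11-20% |

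A 3/12 split was worse, at 16-29%.

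Multivariable models (independence, 600 runs; 1, 5 or 8 patient-level covariates plus a 5/10 centre-level term) gave:

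| ICC | Size CV | Patient-level | Centre-level 5/10 |
|---|---|---|---|
| 0.0044 | 0 | 5.8-8.7% | 10.2-11.7% |
| 0.0044 | 0.6 | 8.9-9.7% | 12.5-14.2% |
| 0.0044 | 1.0 | 9.5-10.9% | 16.2-21.3% |
| 0.02 | 0 | 8.1-9.3% | 9.2-12.3% |
| 0.02 | 0.6 | 8.2-10.0% | 13.3-16.7% |
| 0.02 | 1.0 | 10.7-11.7% | 17.5-21.8% |

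The lone 5.8% is a one-covariate model, with Monte Carlo standard error about √(0.08 × 0.92/600) = 1.1 points. With 14 or 16 centres (ICC 0.0044, CV 0 or 0.6, 3,000 runs) the rates were 7.6-9.6% (patient-level) and 10.1-12.4% (centre-level). A separate simulation over ICC 0.0044-0.05 gave about 8-12% and 8-14%.

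**Remedies, same settings.**
- Mancl-DeRouen-type correction with t on 15 - 2 = 13 degrees of freedom: patient-level 3-6.6%; centre-level 3.7-6.7% (5/10 or 7/8 split) and 6.6-8.4% (3/12).
- Uncorrected sandwich with t on 14 degrees of freedom: patient-level about 5-13%, centre-level about 7-17%. This is not enough.
- Exchangeable model-based errors: patient-level about 4-6%, centre-level 9-14%.

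**The case against.** The strongest reply is that the article never specifies the analysis being criticised. It states no sandwich estimator, normal reference or cluster unit, such details are commonly left to an analysis plan, and mixed models are already on offer. That stands as far as it goes: a reader might infer that the planned tests will have inflated error, or that the false-discovery control fails outright, and the text supports neither. What remains is that GEE is endorsed for centre clustering with no condition, and its ordinary form fails at this number of clusters.

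GEE could instead be clustered on patients with centre as a fixed effect, giving thousands of clusters. That would protect patient-level predictors, but the fixed effects would absorb any centre-level predictor. Clustering on patients without a centre term ignores the centre.

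Other limits stand:
- A reader might quote one range, such as 9-15%, for both kinds of predictor. It does not fit: patient-level rates are nearer 8% with equal centres, while centre-level rates can pass 15%.
- No federal-versus-regional comparison is announced. The 5/10 split only illustrates a centre-level predictor, though the research question does include environmental situations.
- Fifteen is the length of two open lists, not a stated count.
- The simulated outcome is a once-recorded binary death. Time to recovery and other time-to-event outcomes are assigned to Cox or parametric survival models, so the figures do not carry over to them.

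**Conclusion.** The point holds in conditional form. If GEE is clustered on about 15 centres with uncorrected sandwich errors and a normal reference, nominal 5% tests run at about 8-12% for patient-level and about 8-20% for centre-level predictors; very lopsided centre splits or very unequal centres can go beyond these ranges. The direction does not depend on a large assumed ICC, since it appears at the 0.0044 implied by the plan's own design effect. The size rests on assumed centre-size imbalance, on the split, and on a binary outcome recorded once per patient. Whether the inflation will occur cannot be told from the article; the wording permits it, and nothing else in the plan would correct it.

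**What to change.** Replace the open alternative with a default and a condition:
- For the regression outcomes, use a mixed-effects model with a random intercept for centre. Add a patient intercept only for repeatedly measured outcomes; it cannot be identified from one death record per patient. Use small-sample degrees of freedom for centre-level terms.
- If GEE is used with centre as the cluster, require a bias-corrected sandwich (Mancl-DeRouen or Kauermann-Carroll) with a t reference based on the number of centres, for example 13 degrees of freedom for one centre-level contrast among 15.

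The cost is about one sentence of analysis wording and standard software options, with no change to data collection. The downside is somewhat wider intervals. For a very unbalanced centre-level contrast, such as 3 against 12, even the corrected test ran at 6.6-8.4%, so such results should be read with caution.
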